**Figure 2 F2:**
[figure not shown]
Location of P6 acupoint and sham acupoint.

**Table 1 T1:** Details of interventions

**Group names**	**Acupoints**	***De qi *****sensation**	**Interventions**
Acupuncture group	P6 (Neiguan) bilaterally	Yes	P6 at both sides is punctured perpendicularly to a depth of 20 mm. Needles are retained for 30 minutes and stimulated every 10 minutes to keep the *de qi* sensation.
(group A)			
Sham-acupuncture control group	Sham points bilaterally	No	The sham point is punctured to a perpendicular depth of 5 mm bilaterally. Needles are retained for 30 minutes and no stimulation is performed during this duration.
(group SA)			
TENS group	P6 (Neiguan) bilaterally	Yes	P6 acupoint at both sides is stimulated by active self-adhesive electrodes for 30 minutes. The stimulation frequency is set on 2 to 100 hertz and intensity varies until the patients continue to feel the *de qi* sensation.
(group T)			
Placebo-TENS control group	P6 (Neiguan) bilaterally	No	Inactive self-adhesive electrodes are placed at the P6 acupoint bilaterally for 30 minutes.
(group PT)			
Usual treatment group	—	—	—
(group U)			

TENS, transcutaneous electrical nerve stimulation.

For the acupuncture group (group A), after skin cleaning with 75% alcohol swab, sterile and disposable stainless steel needles (0.25 × 25 mm, Wuxi Jiajian, Jiangsu, China) are quickly and perpendicularly inserted into the skin at P6 acupoints bilaterally to a depth of 20 mm. In this group, downward pressure and upward lifting combined with twirling the needle will be used to achieve *de qi* sensation. The needles will be kept in place for 30 minutes and manipulated manually every 10 minutes to maintain the *de qi* sensation. When the treatment time is over, all needles will be carefully taken out and the puncture sites will be covered with sterile swabs to avoid bleeding.

For the sham-acupuncture control group (group SA), sham points are used, which are superficial, non-acupoints on the radial side of each wrist, 15 mm away from each P6 acupoint (Figure 2). After skin cleaning with 75% alcohol swab, sterile and disposable stainless steel needles (0.25 × 25 mm, Wuxi Jiajian, Jiangsu, China) are quickly and perpendicularly inserted into the skin at sham acupoints bilaterally to a depth of 5 mm. The *de qi* sensation is not required in this group. The needles will be retained for 30 minutes as with the group A, but will not be stimulated or manipulated for the duration. After 30 minutes, the same method will be used to take out the needles as in the group A.

For the TENS group (group T), the patients' forearms are cleaned with 75% alcohol swabs and self-adhesive electrodes are placed over P6 acupoints bilaterally. SDZ-V nerve and muscle stimulators (Hwato, Jiangsu, China) are used for TENS (Figure 3). The treatment time is also 30 minutes, using dilatational wave. The stimulation frequency is set on 2 to 100 hertz and intensity varies until the patients feel the *de qi* sensation continuously. The screen on each stimulator is covered with 6 × 8 cm black tape so that no one will see the screen and know whether the stimulator is on or off. When the treatment time is complete, all self-adhesive electrodes will be removed.

**Figure 3 F3:**
[figure not shown]
The SDZ-V nerve and muscle stimulator (Hwato, Jiangsu, China) and self-adhesive electrodes.

For the placebo-TENS control group (group PT), patients have self-adhesive electrodes placed over P6 acupoints bilaterally, and are connected to the SDZ-V nerve and muscle stimulators for 30 minutes. However, as a placebo control group, the stimulators will not be turned on and there will be no electrical stimulation during the treatment. In order to blind patients in this group, each participant will be informed that special acupoint stimulation is used in the treatment which cannot be felt by human sensory perception. After 30 minutes, all self-adhesive electrodes will be removed as in the group T.

For the usual treatment group (group U), no interventions are undertaken. Patients in this group will be observed by the researchers as a blank control, which will provide a baseline postoperative vomiting rate and nausea score in this study using the same drug prophylaxis.

### Outcome measurement

In our study, outcomes are collected based on previously designed PONV studies [18]. The whole study period covers 24 hours after the surgery. A separate research nurse, who is not involved in the management of patients, will record anesthesia time, surgery time, endotracheal intubation time, patient demographics and preoperative data for each patient. Demographic and preoperative data will include: age, gender, race, weight, height, acupuncture experience, smoking history and CPP. Another blinded observer will record the postoperative data, which will include administration of a rescue antiemetic, patient satisfaction with PONV management, and episodes of vomiting or nausea at 2 hours, 6 hours and 24 hours postoperatively. The physicians will record the use time and dosage of rescue antiemetic for each patient when they request rescue therapy, and the records will be handed over to the observer for assessment. Nausea is a subjective sensation which should be evaluated by the patient, not by the observer. Thus, the observer will request the patients to evaluate their nausea score using a standard visual analogue scale (VAS) (0, no nausea at all; 10, worst imaginable nausea). Vomiting, which is defined as the ejection of contents of the stomach through the mouth, will be reported by the patients and assessed by this blinded observer. Patient satisfaction is not an easy concept to measure. Until recently, there has been no consensus on how to measure this concept. Since satisfaction is multi-faceted and subjective, a questionnaire cannot cover every aspect of a patient’s concerns. Therefore, in this study, patients will be asked about satisfaction with their PONV treatment at 24 hours postoperatively using another 0 (very dissatisfied) to 10 (very satisfied) scale.

The incidence of postoperative vomiting within 24 hours after craniotomy across the five groups is the main outcome we are studying. The secondary outcomes are: 1) proportion of participants with a complete response (no vomiting, no nausea, no rescue antiemetic) during 0 to 2 hours, 2 to 6 hours, 6 to 24 hours and 0 to 24 hours after craniotomy under general anesthesia; 2) assessment of nausea score (severity of nausea) during 0 to 2 hours, 2 to 6 hours and 6 to 24 hours after craniotomy under general anesthesia; 3) assessment of total rescue antiemetic dosage during 0 to 24 hours after craniotomy under general anesthesia; and 4) assessment of satisfaction score (patient satisfaction with PONV management) at 24 hours postoperatively.

### Sample size calculation and statistical analysis

A German prospective observational study published in 2011 demonstrated an overall incidence of PONV in 47% of patients after craniotomy under general anesthesia [4]. The sample size is determined by using PEMS 3.1 with α = 0.05 (two-sided) and β = 0.1 (90% power). In order to demonstrate a 30% absolute reduction in the incidence of PONV, the sample size will be 49 patients for each group. Considering the potential loss and attrition, 60 patients per group, or a total of 300 patients, should be reasonable. If a patient can not complete the study due to death, re-operation, unconsciousness or cognitive impairment, the patient will be considered a lost case and recorded as an occurrence of PONV.

All data will be analyzed by a blinded statistician using PEMS 3.1 at a separate location from the WCHSU. The intention-to-treat principal will be used in the data analysis. Baseline data will be collected and compared first. Different statistics are presented differently, for example, continuous data is presented as mean (± standard deviation). Chi-square test is used to compare the incidence of postoperative vomiting, complete response rate, sex difference and other nominal data. Conversely, the Kruskal-Wallis test is used to compare the nausea score, satisfaction score and antiemetic dosage. Additionally, the Nemenyi test and Scheffé’s method are used for multiple comparisons between groups. A *P* value <0.05 is considered statistically significant.

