The primary objective of this study is to evaluate the efficacy of P6 acupoint stimulation versus placebo, and versus routine antiemetic for the prevention of PONV in patients undergoing craniotomy under general anesthesia. The secondary study objective is to compare the efficacy of invasive acupuncture with non-invasive TENS on P6. We hypothesize that a significantly greater percentage of patients will not vomit in the subsequent 24 hours following craniotomy in the acupoint stimulation groups. Additionally, we expect that the severity of nausea will be decreased in the acustimulation groups, based on subjective patient feedback.

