### Randomization and blinding

The randomization sequence will be computer-generated by independent research staff using software called Package for Encyclopaedia Medical Statistics 3.1 (PEMS 3.1). Stratification will not be used in this trial. After randomization, group assignments will be concealed in light-proof and sealed envelopes. The included participants will be randomly enrolled by sealed envelope and assigned to the acupuncture group, sham-acupuncture control group, TENS group, placebo-TENS control group and usual treatment group, using a 1:1:1:1:1 ratio. Patient allocation will be performed by a clinical assistant, who will be trained in institutional review board policies. All study personnel including the outcome assessors, study participants, data analyst and care providers will be blinded to group assignments.

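### The 90% power is that of one unadjusted two-group test, while the plan makes several adjusted comparisons across five arms; power for each of these is lower, and the method for vomiting is not stated

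*Protocol article*

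**What the plan says.** All the sizing statements are in the Protocol article, section on sample size calculation and statistical analysis. The control rate comes from an observational study that "demonstrated an overall incidence of PONV in 47% of patients after craniotomy under general anesthesia". The error rates are given as "The sample size is determined by using PEMS 3.1 with α = 0.05 (two-sided) and β = 0.1 (90% power", and the result as "In order to demonstrate a 30% absolute reduction in the incidence of PONV, the sample size will be 49 patients for each group". The increase to the final size reads "Considering the potential loss and attrition, 60 patients per group, or a total of 300 patients, should be reasonable". No allowance for more than one comparison is mentioned.

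The same section names the chi-square test for the incidence of vomiting and the Kruskal-Wallis test for nausea score, satisfaction score and antiemetic dosage. It then adds that "the Nemenyi test and Scheffé’s method are used for multiple comparisons between groups", without linking either method to an outcome. On patients who cannot complete the study, it says "the patient will be considered a lost case and recorded as an occurrence of PONV".

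Allocation is to five arms "using a 1:1:1:1:1 ratio" (Randomization and blinding). The Background section states the aim: "The primary objective of this study is to evaluate the efficacy of P6 acupoint stimulation versus placebo, and versus routine antiemetic". It gives acupuncture against TENS as the secondary objective.

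**The concern.** The sample size and the analysis work at different significance levels. The sample size gives one pair of arms the full two-sided 0.05. The analysis compares five arms with a multiplicity procedure, so any one pair must clear a higher bar.

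This matters because the objectives are about pairs. There are two active arms (acupuncture A, TENS T), each with its own sham (SA, PT), and a usual-treatment arm (U). Read arm by arm, the primary objective comprises A vs SA, T vs PT, A vs U and T vs U. A significant five-group chi-square test does not say which of these differ. If the follow-up comparisons have well under 90% power, a real 30-point effect could be reported as not significant and read as lack of efficacy.

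**Working it through.** **Inputs from the article.** Control rate 0.47; absolute reduction 0.30, so active rate 0.17; two-sided α 0.05; power 90%; 49 per arm calculated and 60 per arm planned; five arms. The 47% is a rate of nausea and vomiting together, whereas the main outcome is vomiting alone. That is a separate matter, and the article's own inputs are used here.

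**Step 1: reproduce the 49.** Two-group formula with pooled variance under the null and no continuity correction; mean rate (0.47 + 0.17)/2 = 0.32:

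n = [z_α·√(2 × 0.32 × 0.68) + z_β·√(0.47 × 0.53 + 0.17 × 0.83)]² / 0.30²

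= [1.96 × 0.6597 + 1.2816 × 0.6247]² / 0.09 = (1.2930 + 0.8006)² / 0.09 = 48.7, so **49**.

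The power of this unadjusted test is 90.2% at 49 and 95.1% at 60. The stated figure is therefore right for a single two-group test at the full 0.05.

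**Step 2: critical values with five arms.**
- Bonferroni over four comparisons: α = 0.05/4 = 0.0125, z = 2.498.
- Tukey/Nemenyi type, five groups: 2.728.
- Scheffé, five groups: √(95th percentile of chi-square on 4 df) = √9.488 = 3.080, a two-sided level of about 0.0021 per pair.

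**Step 3: power for one pair, 47% vs 17%.** Power = Φ[(0.30 − c·s₀)/s₁], with s₀ = 0.6597/√n and s₁ = 0.6247/√n. At n = 49, s₀ = 0.0942 and s₁ = 0.0892. At n = 60, s₀ = 0.0852 and s₁ = 0.0806.

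| Procedure | c | 49 per arm | 60 per arm | n per arm for 90% |
|---|---|---|---|---|
| None | 1.960 | 90.2% | 95.1% | 49 |
| Bonferroni, 4 | 2.498 | 76.5% | 86.0% | 67 |
| Tukey type | 2.728 | 68.5% | 79.9% | – |
| Bonferroni, 10 (all pairs) | 2.807 | 65.4% | 77.5% | 79 |
| Scheffé | 3.080 | 54.3% | 68.0% | 90 |

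Simulation with 200,000 runs gives 55.3% and 69.2% for Scheffé. The Scheffé figure depends on the variance used: 61.1% and 73.9% with an unpooled standard error; 47–51% and 61–65% with the variance pooled over all five arms.

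**Step 4: the five-group chi-square test.** On 4 df its power is 88% at 49 and 94% at 60 if one active arm works, and 98% and 99.6% if both do.

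**Step 5: Holm over the four comparisons at 60 per arm** (simulation, 200,000 runs). If both active arms work, power is about 94% for A vs SA and T vs PT and about 93% for A vs U and T vs U; all four are won in about 84% of trials, against about 33% with Scheffé (pairwise pooled variance). If only one active arm works, each true contrast has about 88%. With no adjustment at all, the chance of at least one false positive among the four is about 18%.

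**Step 6: effect of losses.** The 60-per-arm figures assume undiluted rates. As an illustration only, suppose all 11 extra patients in each arm are lost and scored as events. The rates become (49 × 0.47 + 11)/60 = 56.7% and (49 × 0.17 + 11)/60 = 32.2%. Power at 60 is then about 35% with Scheffé and 58% with four-comparison Bonferroni. The article gives no expected loss rate; this shows the direction, not a forecast.

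**The case against.** The strongest reply is that a reader might infer the plan fixes Scheffé's method for vomiting, so that 54–68% is simply the trial's power. The article does not say this. The multiple-comparison sentence follows the Kruskal-Wallis sentence and assigns neither method to an outcome. Scheffé for proportions is inferred from the Nemenyi test being rank-based. This objection stands: 54% and 68% are conditional figures. It does not remove the problem, because every adjustment in Step 3 leaves a pair below 90% at both sizes, and having no adjustment leaves familywise error at about 18% over four tests.

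Second, the test the article does name for vomiting, chi-square across five groups, is adequately powered. That stands too, so a claim that the whole trial is underpowered would be wrong. But this test alone does not settle active against sham or active against usual treatment.

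Third, the four pairs are one reading of the objective; the active arms could instead be pooled. With equal effects in both and the Scheffé value, A+T vs SA+PT has about 93% at 49 and 98% at 60 per arm, and A+T vs U about 77% and 87%. The article does not state a pooled analysis, and its design with a separate sham for each method points to arm-by-arm comparison. The reply does show that the contrasts need to be named.

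Fourth, Scheffé is valid and conservative. That is so: the cost here is lost power, not false positives.

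Finally, detailed post-hoc rules may be left to an analysis plan. The article, however, states both the sizing level and the multiple comparisons in one section, and the two do not match.

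**Conclusion.** The point holds as a mismatch between sizing and analysis. The figure of 49 is not an arithmetic error: it is correct for the calculation described, and the article never claims that the 90% is adjusted for multiplicity. But that 90% does not carry over to the pairwise comparisons the primary objective needs.

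How far power falls depends on a choice the article leaves open. At 49 and 60 per arm it is about 54% and 68% under Scheffé, the likely but unstated choice, and about 69–77% and 80–86% under a Tukey-type or four-comparison Bonferroni adjustment. These figures rest on the article's 47% and 30-point reduction, on arm-by-arm contrasts, on the normal approximation with pairwise pooled variance, and on no losses; losses counted as events would lower them.

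A reader might also conclude that the trial must grow to the 90 per arm that Scheffé would require. That does not follow, because a procedure aimed at the planned comparisons recovers most of the power at 60 per arm.

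**What to change.** 1. Name the primary vomiting comparisons: A vs SA, T vs PT, A vs U and T vs U. Test them with Holm's procedure at a familywise two-sided 0.05, in place of Scheffé.
2. Test A vs T separately, as the stated secondary objective, so that it is not lost from the plan.
3. Replace the single 90% by the multiplicity-adjusted power at 60 per arm: about 88% per true contrast if only one active arm works and about 93–94% if both work. State that these figures are before losses, and that losses lower them because they count as events.
4. Keep 300 patients.

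The cost is a change of analysis wording and a restated power. The article reports that recruitment is still under way, so the change should be fixed and dated before any unblinding. The downside is that contrasts outside the list lose formal protection and become exploratory. Holm also does not guarantee 90% for each contrast: with one effective arm it stays slightly below.

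### Baseline balance is tested and vomiting is then compared crudely; a prespecified analysis adjusted for sex, age and smoking would give a modest, assumption-dependent gain from data already collected

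*Protocol article*

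**What the plan says.** In the Protocol article, Sample size calculation and statistical analysis, the order is set by "Baseline data will be collected and compared first". The same paragraph gives one test for baseline and outcome data alike: "Chi-square test is used to compare the incidence of postoperative vomiting, complete response rate, sex difference and other nominal data". Kruskal-Wallis is assigned to nausea score, satisfaction score and rescue dose. No model with covariates is named, and no use is stated for the result of the baseline comparison.

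Under Randomization and blinding: "Stratification will not be used in this trial". Under Outcome measurement, the variables recorded for each patient include "age, gender, race, weight, height, acupuncture experience, smoking history and CPP".

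The size of the trial comes from "In order to demonstrate a 30% absolute reduction in the incidence of PONV, the sample size will be 49 patients for each group", raised for losses to "60 patients per group, or a total of 300 patients, should be reasonable".

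**The concern.** Two choices deserve a second look.

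**Testing balance.** If allocation was properly random, any baseline difference between arms is due to chance, so a p-value for it answers a question nobody has. The plan attaches no consequence to the result. A nominally significant difference, seen before the outcome analysis and with no adjustment rule in place, leaves the team to decide afterwards whether to adjust.

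**Leaving the covariates unused.** Neither the design nor the stated outcome analysis makes use of prognostic information. Sex, age and smoking history are available for all patients before treatment. If they predict vomiting, an analysis that conditions on them is more precise than the crude comparison. What is at stake is some precision and a cleaner prespecification, chiefly for contrasts smaller than the 30-point design effect. The comparison of acupuncture with TENS, the secondary objective, may be one of these, since both arms are active.

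**Working it through.** **Inputs from the Protocol article:** two-sided α 0.05 (z = 1.960); power 90% (z = 1.2816); 47% against 47 − 30 = 17%; 49 per group before and 60 after the allowance for losses. The 47% is an incidence of PONV, whereas the main outcome is vomiting; it is kept here as the plan's own design rate. All power figures are for one pair of arms at 0.05, as in the plan's own calculation.

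**Input not in the documents:** R², the share of outcome variance explained by sex, age and smoking. Assumed range 0 to 0.20.

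**1. The plan's figure.** With mean rate 0.32:

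n = [1.960·√(2·0.32·0.68) + 1.2816·√(0.47·0.53 + 0.17·0.83)]² / 0.30² = [1.293 + 0.801]² / 0.09 = 48.7, so 49. The stated figure reproduces exactly.

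**2. Crude power at 60 per arm.**
- 30 points: Φ[(0.30·√60 − 1.293) / 0.625] = Φ(1.65) = 95.1%.
- 20 points (47% vs 27%, mean 0.37): Φ[(0.20·√60 − 1.338) / 0.668] = Φ(0.316) = 62.4%.

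**3. Power with adjustment, by approximation.** Replace 60 by 60 / (1 − R²) in step 2.

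| Assumed R² | Effective n per arm | Power, 30 points | Power, 20 points |
|---|---|---|---|
| 0 | 60 | 95.1% | 62.4% |
| 0.05 | 63.2 | 96.0% | 64.7% |
| 0.10 | 66.7 | 96.8% | 67.0% |
| 0.20 | 75 | 98.2% | 72.2% |

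Put another way, the 49 needed becomes 49 × 0.95 = 46.6 at R² 0.05 and 49 × 0.90 = 44.1 at R² 0.10.

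**4. Check by simulation.** Two arms of 60, 1,500 runs per scenario. The crude two-proportion test was compared with a logistic model on arm, sex, smoking and age (likelihood-ratio test). The variance ratio is that of the standardised risk difference to the crude one, over effects of 0, 20 and 30 points. Covariate strengths are assumed.

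| Covariates (control-arm R²) | Variance ratio, adjusted/crude | Power, 30 points, crude → adjusted | Power, 20 points, crude → adjusted |
|---|---|---|---|
| Not prognostic (0) | 1.02-1.03 | 95.1 → 95.3% | 61.1 → 60.8% |
| Weak (0.02) | 0.99-1.03 | 96.3 → 95.9% | 62.3 → 63.5% |
| Moderate (0.09) | 0.94-0.97 | 95.5 → 96.3% | 65.0 → 68.5% |
| Strong (0.19) | 0.83-0.88 | 95.0 → 97.5% | 62.3 → 70.5% |

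Type I error was 4.2-5.5% crude and 4.5-5.7% adjusted; the simulation standard error is √(0.05·0.95/1500) = 0.56 points. Both tests hold their level.

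Step 3 is slightly generous on variance. At R² 0.09 it implies a ratio of 0.91, while the simulation gives 0.94-0.97, because the covariates explain less in an arm with fewer events and because estimating them has a small cost.

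**5. Is chance imbalance outside the crude standard error?** Assume half the patients are women and that women vomit 20 points more often than men. The 95% chance range for the difference in sex mix between two arms is 1.96·√(2·0.25/60) = ±17.9 points, which moves the vomiting contrast by 0.179 × 0.20 = 3.6 points. The crude 95% half-width at 47% in both arms is 1.96·√(2·0.47·0.53/60) = 17.9 points. Sex therefore contributes (3.6/17.9)² = 4% of a variance that the crude test already counts in full.

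**The case against.** The strongest reply is that nothing here is wrong. An unadjusted chi-square after unstratified randomisation is valid, the simulation confirms its error rate, and an adjusted analysis may sit in an analysis plan that is not shown. The design power is already 95.1%, so little is left to gain there. The documents give no prognostic strength for sex, age or smoking. The eligibility criteria narrow risk (no history of PONV or motion sickness, ASA I or II). Lost cases are recorded as PONV; if that rule also applies to vomiting, some events may be unrelated to these covariates, which would dilute the gain.

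Most of this stands, and it limits the point to an improvement. It does not remove it: the article itself names the crude test for the main outcome and a significance test for sex, so a method is stated and a better one can be put in its place.

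Three stronger readings are tempting and are not supported:

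- **That imbalance biases the vomiting contrast.** Step 5 shows that it is ordinary random error already inside the crude standard error.
- **That adjustment is a sure gain.** With covariates that do not predict vomiting, it costs about 2-3% in variance.
- **That each of the eight listed baseline variables will be tested, making a false alarm likely.** Acupuncture experience is fixed at none by the inclusion criteria, race will hardly vary among Chinese patients, and no baseline test is named for age, weight, height or CPP. The text supports a test only for sex and other nominal data.

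Nor does the article contain a rule that makes adjustment depend on the baseline result. The risk of a data-driven choice is an opening left by the plan, not a stated procedure.

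**Conclusion.** The point holds as a low-cost improvement in precision and prespecification. The planned test is valid and the trial's conclusion is not threatened. If sex, age and smoking history explain 5-10% of outcome variance, pairwise power at 60 per arm rises by about 1-2 points at the 30-point design effect and by about 2-5 points at a 20-point effect. If they explain nothing, variance may rise by about 2-3%. These figures rest on the assumed R², on 47% as the control rate for vomiting, and on a single pairwise comparison at 0.05. The case against significance testing of baseline balance rests on none of these: under proper randomisation such a test informs no decision, whatever the covariates are worth.

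**What to change.** 1. Replace the baseline significance tests with a descriptive table by arm, and delete the sex comparison from the list of chi-square tests.
2. Before unblinding, prespecify for vomiting and complete response a logistic model with arm, sex, age and smoking history. State how each covariate is coded, and report a standardised risk difference with 95% CI for each planned contrast. Naming the risk difference avoids confusion between a conditional odds ratio and the absolute reduction on which the sample size is based.
3. Keep the crude chi-square as a sensitivity analysis, and state that no covariate will be added or dropped in response to the observed baseline data.

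Cost: wording in the analysis plan and slightly more analysis work, with no new data, patients or procedures. The article does not say whether PEMS 3.1 can fit and standardise such a model, so other software may be needed. If the covariates turn out not to be prognostic, the precision loss is negligible. The Trial status section reports that recruitment is under way, so the change can still be made before unblinding.

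### The only test clearly assigned to vomiting compares all five arms at once, so it does not answer P6 versus placebo or P6 versus usual care

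*Protocol article*

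**What the plan says.** All references are to the protocol article.

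- **Objective (Background).** "The primary objective of this study is to evaluate the efficacy of P6 acupoint stimulation versus placebo, and versus routine antiemetic". The hypothesis that follows is directional: "a significantly greater percentage of patients will not vomit in the subsequent 24 hours following craniotomy in the acupoint stimulation groups".
- **Main outcome (Outcome measurement).** "The incidence of postoperative vomiting within 24 hours after craniotomy across the five groups is the main outcome we are studying".
- **Test (Sample size calculation and statistical analysis).** "Chi-square test is used to compare the incidence of postoperative vomiting, complete response rate, sex difference and other nominal data". Scores and antiemetic dose get a Kruskal-Wallis test. The section then adds: "Additionally, the Nemenyi test and Scheffé’s method are used for multiple comparisons between groups". Significance is P < 0.05, with no division among comparisons.
- **Sample size (same section).** 49 per group for a 30-point absolute reduction from 47%, two-sided 0.05, 90% power, raised to 60 per group (300 in total) for losses.
- **Arms (Interventions and Table 1).** Acupuncture (A), sham acupuncture (SA), TENS (T), placebo TENS (PT) and usual treatment (U). Every patient receives ondansetron before skin closure. Group U gets no further intervention, "which will provide a baseline postoperative vomiting rate and nausea score in this study using the same drug prophylaxis".

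**The concern.** The objective, the outcome definition and the test do not fit together. The objective names two directed questions: does P6 beat its placebo, and does it beat usual care? A chi-square test across five arms asks only whether any arm differs from any other. A significant result could come from a non-specific response to being treated, since group U alone receives no procedure. It could also come from one sham arm behaving differently. In neither case does it show that P6 works better than placebo.

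The sample size is a two-group calculation, so the trial appears to be sized for a pairwise contrast that the analysis section never names. What is at stake is whether the main P value can support the main claim.

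A related wording problem is that all arms receive ondansetron, so no arm sets P6 against an antiemetic. The contrast with group U estimates P6 plus ondansetron against ondansetron alone.

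**Working it through.** **Inputs.** From the article: 47% control rate, 30-point reduction (so 17%), two-sided 0.05, 90% power, 49 and 60 per group, 1:1:1:1:1 allocation. Assumed here: the arm-by-arm vomiting rates in step 2, built around 47% and 17%. (The 47% is a PONV rate, used here as the article uses it.)

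**1. The plan's own figure.** Two proportions, pooled variance, no continuity correction, mean rate 0.32:

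n = [1.960·√(2·0.32·0.68) + 1.282·√(0.47·0.53 + 0.17·0.83)]² / 0.30² = 48.7, so 49.

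The stated 49 is reproduced exactly, as a two-group comparison. Power for one pair at 0.05 is 90.2% with 49 per group and 95.1% with 60.

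**2. What the five-group test detects.** Pearson chi-square on the 2×5 table, critical value χ²(0.95; 4 df) = 9.488, 60 per arm, 100,000 simulated trials per scenario. Pairs are tested unadjusted at 0.05.

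| Assumed vomiting rates | Five-group test | A vs SA | T vs PT | A vs U | T vs U |
|---|---|---|---|---|---|
| A, SA, T, PT 27%; U 47% | 65.0% | 5.1% | 5.4% | 62.8% | 63.0% |
| A, SA, T, PT 17%; U 47% | 97.8% | 4.7% | 4.8% | 95.3% | 95.3% |
| SA 17%; all others 47% | 96.8% | 95.5% (A worse than SA) | 5.4% | 5.4% | 5.4% |
| A, T 17%; SA, PT, U 47% | 99.8% | 95.4% | 95.5% | 95.4% | 95.4% |

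First row by formula: mean rate (4·0.27 + 0.47)/5 = 0.31. The non-centrality is 60·[4·(0.04)² + (0.16)²]/(0.31·0.69) = 60·0.032/0.2139 = 8.98, which gives 66% and agrees with the simulation.

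The test rejects almost as often in rows 2 and 3 as in row 4, which is the effect the trial hopes for. Its P value cannot tell these situations apart.

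**3. Whether the Scheffé step rescues it.** Applied to pairs of proportions among five groups, the Scheffé critical value is √9.488 = 3.080. At 60 per arm:

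power = Φ{[0.30·√60 − 3.080·√(2·0.32·0.68)] / √(0.47·0.53 + 0.17·0.83)} = 68.0%; simulation gives 69.0%.

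With 49 per arm the formula gives 54.3%. If the four pairs are instead tested at 0.05 without adjustment, the chance of at least one false positive with all arms at 47% is about 18% (simulated).

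**4. Four named contrasts.** Holm's first step is 0.05/4 = 0.0125, critical value 2.498. Power for 47% against 17% with 60 per arm is 86.0% by the same formula and 86.9% by simulation. It is 76.5% with 49. Reaching 90% at that step needs 67 per arm.

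**5. A pooled alternative.** Mantel-Haenszel active against sham, stratified by modality (120 vs 120), at 0.05: 99.9% power if both modalities move from 47% to 17%, and 90% if both fall by 20 points. If only acupuncture works (47% to 17%), pooled power is 68%, against 95% for A vs SA alone.

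**The case against.** **Pairwise comparisons are planned.** A reader might infer from the chi-square sentence that nothing else is done. The Nemenyi and Scheffé sentence shows otherwise, and this part of the objection stands. It does not close the gap: the sentence is not linked to vomiting, names no contrasts, and cites procedures that in their usual form are for rank sums and means.

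**The five-group test is inferred.** The test sentence gives no number of groups, and the article labels nothing as the primary test. The 49 per group even points towards pairs. This is fair, but the outcome definition and the parallel Kruskal-Wallis test make the five-group reading the natural one. If pairs were meant, they are not named.

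**A placebo response is not a null result for P6.** A reader might infer that the 65% figure shows significance with no P6 effect at all. It does not: with U at 47% and both P6 arms at 27%, P6 truly beats usual care by 20 points, which is half of the stated objective. That scenario shows only no effect beyond sham. The scenario with sham acupuncture alone lower is the one in which P6 beats no comparator.

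**The adjunct role is already clear.** The article says that all arms receive ondansetron and calls P6 an adjunct. The intent can be recovered, so the objective's wording is the only thing to change there.

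**An analysis plan may list the contrasts.** One may exist and is not shown. The point rests on what the article does fix: an objective, an outcome, a test and a sample size that do not match.

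**Conclusion.** The point holds. On the natural reading, the only test clearly assigned to vomiting does not answer the primary objective. With 60 per arm it is significant in about 65% of trials when P6 is no better than sham (27% in all four intervention arms, 47% in U) and in about 97% when only sham acupuncture is lower. Both figures rest on assumed rates. The follow-up procedures, taken literally, give about 68 to 69% power per pair for the planned effect rather than 90%.

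The documents do not support saying that between-group testing is absent. Nor do they support saying that a pooled active-against-sham test must be primary. The article expects that acupuncture may outperform TENS, and the two shams differ (superficial needling away from P6; inactive electrodes on P6). Separate contrasts are therefore a legitimate choice, and pooling loses power if only one modality works.

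**What to change.** 1. Base the primary conclusion on four named contrasts of 24-hour vomiting proportions: A vs SA and T vs PT (versus placebo), A vs U and T vs U (versus usual care). Use two-group chi-square tests with Holm adjustment, and report each risk difference with a 95% CI. These replace the five-group test and Nemenyi/Scheffé for this outcome.
2. Restate the power: about 86 to 87% per contrast for 47% against 17% at 60 per arm at the strictest Holm step, in place of 90%.
3. Optionally add the modality-stratified Mantel-Haenszel test of active against sham as supportive.
4. Reword the second half of the primary objective as P6 stimulation plus ondansetron versus ondansetron alone.

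The cost is wording only, with no new data. The article reports that recruitment is still open; the contrasts should be fixed before any unblinded data are seen. The downside is the modest loss of power per contrast in item 2.
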